### Sample size

The required sample size will be determined on the basis on the functional capacity, using the Short Physical Performance Battery (SPPB) [42]. According to previous research on subjects with similar characteristics [17], a clinically relevant change is about 1.5 ± 1.0 points increments after 12-weeks. Differences of 2 point in total SPBB with a standard deviation of 3 points with a power of 80% and α of 0.05 can be estimated with 20 participants using the R software (v. 3.2.1) and the package *samplesize*. Assuming a maximum loss of follow-up of 30%, we will recruit 26 adults ≥70 years per group (*n* = 104). Similar interventions had an adherence rate of 75%, and a mean attendance of 80% to the sessions [17]. Therefore, the current estimation is realistic and affordable.

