### Randomization and blinding

After recruitment and baseline measurements, nursing home will be randomized to either of the four groups in clusters, according to a computer-generated sequence using the Sealed Envelope Ltd. online system. The cluster design is chosen to prevent influences on participants’ behaviours within a given nursing home unit. A stratified randomization will be used according to their initial functional status (A, B, C or D, see Fig. 2) to reduce imbalance between groups. The allocation will be concealed in a password protected computer file. Given the nature of the treatment (i.e., daily exercise and dietary supplementation program), participants will be aware of their group allocation. Outcome assessors and data analysts will be blinded to the treatment group assignment. Assessors will not be involved in intervention activities. A dedicated protocol will be defined to protect the confidentiality of data.

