#### Multicomponent physical exercise program

Intervention groups including exercise (Ex-HMB and Ex-Plac) will complete an individualized multicomponent training program, VIVIFRAIL [16], 5 days a week during 24 weeks. Free on-line resources and program guidelines are available online (http://www.vivifrail.com/resources). The VIVIFRAIL program has been carefully designed for people ≥70 years and includes six programs or “Passports” adapted for each participant’s condition according to their functional limitation (serious [A], moderate [B], slight [C] and no limitation [D]) and risk of falling (B+ and C+). Individualization is made based on the baseline testing scores (i.e., the VIVIFRAIL test). Each program combines strength, power, balance, walking, stretching and cardiovascular exercises, in the named “VIVIFRAIL Wheel”. Training sessions are daily and weekly organized (type of exercise, steps and reps) in individual “Passports”. A summary of the exercise program is shown in Fig. 2.

The VIVIFRAIL program has a free mobile app available on iOS and Android, the latest version of which, (launched in January, 2019) allows the recording of the results of the test to automatically assign each participant to a training program. The App includes a calendar with a daily progression, training monitoring and rate of perceiving effort assessment.

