### Outcome measures

*Functional capacity (primary outcome):* The Short Physical Performance Battery (SPPB) [42] scores from 1 (low mobility) and 12 (full mobility) points based on three tests: balance tests (tandem, semi-tandem and one foot next to the other), gait speed and 5-sit-to-stand test. The SPPB has been extensively administrated in older adults [17, 44]. The resulting scores are part of the VIVIFRAIL test to determine each individual’s physical exercise program [16].

*Maximal muscle strength and power output:* grip strength measurement (Jamar digital dynamometer, NexGen ergonomics, Pointe Claire, Quebec, Canada) [45], one repetition maximum (1RM) seated leg press and vertical bench press strength (Salter Ltd., Barcelona, Spain) and muscle power (T-Force Dynamic Measurement System, Ergotech Consulting SL, Murcia, Spain) [46, 47], sit-to-stand muscle power [48], in the same order with a 3-min rest between tests in order to diminish fatigue [49].

*Frailty and fall risk*: frailty phenotype determination [50], complete falls history and fall risk assessment, physical examination [16].

*Body composition:* Body composition will be assessed using dual-energy x-ray absorptiometry - DXA (Hologic, Bedford, MA; Discovery A), between 6:00 AM and 9:00 AM after a ≥ 10-h fast and after participants had voided their bladders [51].

*Blood pressure and resting heart rate:* Systolic and diastolic blood pressure, as well as resting heart rate will be measured after 10 min of rest, two times 2 min apart (M6 upper arm blood pressure monitor Omron. Omron Health Care Europe B.V. Hoofddorp, The Netherlands).

*Haematology*: Erythrocyte count, haematocrit, haemoglobin, platelets, leukocytes and erythrocyte mean corpuscular volume will be quantified by Coulter Cell Counter.

*Biochemical analyses*: glucose, high-density lipoprotein (HDL), total cholesterol (TC), triglycerides (TG), glycosylated haemoglobin (HbA_1c_), thyroid-stimulating hormone (TSH), C-reactive protein (CRP), albumin, prealbumine, transferrin, insulin-like growth factors (IGF-1 and IGFBP-3), creatine phosphokinase (CPK) and 25-hydroxyvitamin D (25[OH]D). Blood analysis will be conducted with standard methods using an autoanalyzer. Insulin sensitivity will be derived from the homeostatic model assessment for insulin resistance (HOMA-IR).

*Nutritional status:* The Mini-Nutritional Assessment (MNA-SF) [52] will be used to evaluate nutrition status and malnutrition risk.

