### Statistical analysis

Analysis will be performed on participants who attended at least 80% the training sessions and completed all the measurements. Treatment effects will be tested using generalized linear models. All models will be adjusted for the baseline outcome value and repeated adjusting for gender, age, the group effect, and confounding factors.

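### Randomisation is stratified by functional class A–D, but class is absent from the first analysis model and not named in the repeated one; adding it would gain modest precision, mainly for secondary outcomes

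*Protocol article*

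**What the plan says.** All references are to the protocol article.

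- **Unit of allocation** (Randomization and blinding): "nursing home will be randomized to either of the four groups in clusters".
- **Stratification** (same section), with one factor only: "A stratified randomization will be used according to their initial functional status (A, B, C or D, see Fig. 2) to reduce imbalance between groups".
- **What class is** (Multicomponent physical exercise program): a resident's degree of functional limitation, from serious (A) to none (D), taken from the baseline VIVIFRAIL test.
- **Link to the primary outcome** (Outcome measures, on SPPB): "The resulting scores are part of the VIVIFRAIL test to determine each individual’s physical exercise program".
- **Model** (Statistical analysis): "Treatment effects will be tested using generalized linear models". The covariates follow: "All models will be adjusted for the baseline outcome value and repeated adjusting for gender, age, the group effect, and confounding factors".
- **Analysed set** (same section): residents with at least 80% session attendance and complete measurements.

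The covariate sentence describes two models. The first adjusts for the outcome's baseline value. The second repeats it with gender, age, a group effect and confounding factors that are not listed. Functional class is named in neither.

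**The concern.** A factor chosen for stratification is normally one expected to predict outcome. If the allocation balances it, the treatment estimate varies less than a model without the factor assumes, so the reported standard error is too large and power is lost. If the allocation does not balance it, a model without the factor leaves the chance difference between arms in the estimate. Including the factor helps in both cases.

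The outcome's own baseline value can stand in for class only where the two overlap. For SPPB they overlap by construction. For grip strength, 1RM, Barthel index, MMSE, depression or body composition, the baseline value need not carry the information in class. At stake is some precision on those secondary outcomes, from a covariate already known for every resident before allocation.

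**Working it through.** **Plan's own figure.** The article gives no figure for the prognostic value of class, so there is none to reproduce. From Sample size I take 20 evaluable residents per group and a difference of 2 points with SD 3, that is 2/3 = 0.667 SD. (The stated 20 matches a one-sample or paired two-sided t-test, power 80.7%. A two-group t-test with 20 per group has 53.8%, which is why the powers below sit near 55%. That is a separate matter.)

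**Assumption.** Let p be the share of the outcome variance left after the baseline value that class explains. The documents do not give p; I use 0 to 30%.

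**Step 1: formula, class exactly balanced across residents, no clustering.** Set the residual variance to 1.
- Reported standard error without class: √(2/20) = 0.316.
- Actual standard error: √(2(1−p)/20).
- Ratio: 1/√(1−p).
- Approximate two-sided type I error: 2Φ(−1.96/√(1−p)).

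| p | Ratio | Type I error |
|---|---|---|
| 0 | 1.000 | 5.0% |
| 5% | 1.026 | 4.4% |
| 10% | 1.054 | 3.9% |
| 20% | 1.118 | 2.8% |
| 30% | 1.195 | 1.9% |

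**Step 2: simulated ANCOVA.** Four arms of 20, five residents per class per arm, effect 0.667 residual SD, 4,000 null trials and 3,000 with the effect.

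| p | Reported SE, no class | Actual SD | Type I error, without / with class | Power, without / with class |
|---|---|---|---|---|
| 0 | 0.317 | 0.322 | 5.2% / 5.3% | 55.4% / 54.9% |
| 5% | 0.318 | 0.312 | 4.9% / 5.4% | 55.4% / 57.6% |
| 10% | 0.318 | 0.301 | 3.7% / 5.0% | 52.8% / 56.9% |
| 20% | 0.319 | 0.292 | 3.3% / 5.6% | 53.8% / 63.2% |
| 30% | 0.320 | 0.267 | 2.0% / 5.0% | 53.0% / 68.4% |

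The overstatement of the standard error runs from 0.318/0.312 = 1.02 at 5% to 0.320/0.267 = 1.20 at 30%, in line with step 1. The power loss runs from about 2 to 15 points. The simulation error on a type I error near 5% is √(0.05×0.95/4000) = 0.34 points. A second simulation with two arms, baseline correlation 0.7 and effect 0.65 SD gave power losses of about 1 to 9 points for the same values of p. The power loss therefore depends on the set-up; the direction does not.

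**Step 3: homes randomised, class not forced into balance.** Assumed: 12 homes, three per arm, 20 residents per arm, mild clustering of class within homes, no home term in the model, 3,000 trials.

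| p | ICC | Actual SD, without / with class | Type I error, without / with class |
|---|---|---|---|
| 0 | 0 | 0.314 / 0.323 | 4.4% / 5.0% |
| 0 | 0.05 | 0.365 / 0.372 | 8.6% / 8.3% |
| 0 | 0.10 | 0.397 / 0.402 | 11.8% / 11.2% |
| 10% | 0 | 0.334 / 0.318 | 6.5% / 5.6% |
| 10% | 0.05 | 0.371 / 0.356 | 9.5% / 9.2% |
| 10% | 0.10 | 0.405 / 0.392 | 13.3% / 12.4% |
| 20% | 0 | 0.326 / 0.288 | 6.2% / 4.5% |
| 20% | 0.05 | 0.366 / 0.340 | 9.5% / 9.7% |
| 20% | 0.10 | 0.407 / 0.373 | 13.5% / 13.1% |

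Two things follow. Class still reduces the true spread of the estimate where it is prognostic: at p = 10% by 3–5% (for example 0.392/0.405 = 0.968), at p = 20% by 7–12%. Where it is not prognostic, it costs 1–3%. With an ICC of 0.05 or 0.10, however, type I error stays at about 8–13% with class in the model. Class adjustment does not deal with clustering.

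**The case against.** **The covariate list is open, and an article condenses a fuller plan.** Confounding factors could include class, and an analysis plan not shown may name it. A reader might infer that the trial excludes class from every analysis; the text does not say so. This stands for the repeated model. It does not reach the first model, where the only stated adjustment is the outcome's baseline value.

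**Balance on class is not assured.** Homes are randomised, class belongs to the resident, and the article does not say how a home is placed in a class stratum. Restricting the analysis to adherent completers can disturb whatever balance there was. A reader might infer from step 2 that this trial's standard errors will be too large and its type I error 2–4%. The documents do not support that: those figures need exact balance across individual residents and no clustering. Under home randomisation, step 3 shows error at or above 5% in nearly all settings without class, and adding class barely changes it once there is clustering. This objection stands, and it limits the point to lost precision and uncorrected imbalance.

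**The size is assumed.** No document supports a share of 20–30% for, say, MMSE or body composition once their own baseline is in the model. This stands; at 0% there is nothing to gain.

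**Class sets the programme only in the two exercise groups.** That suggests effect modification, which a main-effect covariate does not address. This also stands, so I do not rest the point on it.

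**Conclusion.** The point holds in a limited form. The only stratification factor is missing from the first model and unnamed in the second. If class is balanced and prognostic beyond the outcome's baseline, reported standard errors are about 2–20% too large for an assumed share of 5–30% of residual variance, with some loss of power and no effect at 0%. If class is not balanced, chance differences between arms go uncorrected.

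Under balance the omission is conservative, so it should not be read as creating false positives. For SPPB the effect is probably small. Severity is minor: a near-free improvement for secondary outcomes. The class share, the ICC and the number of homes are all assumptions. The absence of any named nursing-home effect is a separate and larger threat to the standard errors, and it acts in the opposite direction.

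**What to change.** In Statistical analysis, state that the main model for every outcome includes the resident's baseline functional class (A, B, C, D) as a fixed covariate, alongside the outcome's baseline value, whether or not balance was achieved. In Randomization and blinding, add a sentence on how class was applied when homes were randomised, so that the stratification and the model can be matched.

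The cost is a phrase in one section, a sentence in another, and three degrees of freedom. With 80 residents analysed, the first model has 80 − 5 = 75 residual degrees of freedom (four arm means and one baseline slope), and 72 with class. Class comes from baseline testing before allocation, so no new data are needed. Accounting for the nursing home has to be settled separately; this change does not substitute for it.

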### Recruitment process and measurements procedures

A schematic overview of the outcomes, measures and timeline is shown in Table 2. Recruitment will be carried out in nursing homes in Murcia (Spain) located within a radius of 15 km or less than 20 min by car from the assessment sites. There are over 15 nursing homes among this radius that ensure recruitment of enough participants. Initial assessment will be carried out in the Human Performance & Sports Science Lab, Faculty of Sport Sciences, University of Murcia (Murcia, Spain). Body composition and biochemical analyses will be performed in the Medical Centre Virgen de la Caridad (Murcia, Spain). Participants will be scheduled in small groups to be taken to the laboratory for the initial assessment and medical centre. Dependent people will be transported in adapted vehicles with a caregiver. All measurements will be performed under technical and medical supervision.

**Table 2 Tab2:** Schedule of enrollment, interventions, and assessments

TIMEPOINT	Enrollment -t_1_	Allocation 0	Baseline t_1_	Intervention	Follow-up 12th week post baseline t_2_	Close-out 25th week post baseline t_3_
ENROLLMENT						
Eligibility screen	✓					
Informed consent	✓					
Randomized Allocation		✓				
INTERVENTION				✓		
Ex-HMB				✓		
NoEx-HMB				✓		
Ex-Plac				✓		
Control				✓		
ASSESSMENTS						
*Functional capacity (primary outcome)*						
SPPB: Gait speed, balance, and 5-sit-to-stand	✓		✓		✓	✓
*Muscle strength and power*						
Grip strength			✓		✓	✓
1RM seated leg press			✓		✓	✓
1RM vertical bench press			✓		✓	✓
Sit-to-stand muscle power			✓		✓	✓
*Frailty and fall risk*						
Frailty phenotype			✓		✓	✓
Falls history	✓		✓		✓	✓
Fall risk assessment	✓		✓		✓	✓
*Body composition*			✓			✓
*Blood pressure and resting heart rate*			✓		✓	✓
*Haematology*			✓		✓	✓
*Biochemical analyses*			✓		✓	✓
*Nutritional status*			✓		✓	✓
*Sarcopenia*			✓		✓	✓
*Disability and comorbidity*						
Barthel index			✓		✓	✓
Lawton index			✓		✓	✓
Comorbidity			✓		✓	✓
*Cognitive function*	✓		✓		✓	✓
*Depression*			✓		✓	✓

Ex: 12-week of VIVIFRAIL multicomponent exercise program. HMB: dietary supplementation of HMB. *Plac* Placebo. *SPPB* Short Physical Performance Battery; *1RM* one-repetition maximum

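### SPPB is scheduled twice before the intervention but the model adjusts for one baseline value: valid, but slightly less precise than the scheduled measurements allow

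*Protocol article*

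**What the plan says.** In the protocol article, Table 2 (under Recruitment process and measurements procedures) has separate columns for enrollment, allocation and baseline. The row "SPPB: Gait speed, balance, and 5-sit-to-stand" is ticked at enrollment, baseline, week 12 and week 25, and the cognitive function row likewise. Most other outcomes are first ticked at baseline; falls history and fall risk also carry both early ticks.

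On timing, the Randomization and blinding section states: "After recruitment and baseline measurements, nursing home will be randomized". On that wording, both early SPPB scores precede allocation. Table 2 places its allocation column between enrollment and baseline, so the two places disagree.

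On the model, the Statistical analysis section states: "All models will be adjusted for the baseline outcome value". The value is singular and the rule covers all models. Further adjustment is for gender, age, group and unnamed confounding factors. The enrollment score has no stated role in the analysis.

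**The concern.** Baseline adjustment gains precision by removing variance between residents that was present before treatment. A single score carries test-to-test variation as well as the resident's underlying function. The mean of two scores carries less of that variation and so predicts follow-up somewhat better. If the second score is already collected, leaving it out gives up a little precision and saves nothing.

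The trial has little precision to spare. It plans 26 residents per group and allows for 30% loss, which leaves 26 × 0.7 = 18.2 per group. The analysis set is then limited to residents with at least 80% attendance and complete measurements.

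**Working it through.** **The plan's own figure, for scale.** The Sample size section assumes: "Differences of 2 point in total SPBB with a standard deviation of 3 points", and continues: "with a power of 80% and α of 0.05 can be estimated with 20 participants". For a two-group comparison with two-sided α, n per group = 2 × (1.960 + 0.842)² × 3² / 2² = 35.3, so 36 (37 with the exact t-test). One-sided, it is 28 (29 with the t-test). The stated 20 appears only for a one-sample or paired two-sided t-test (power 0.807). As an unadjusted two-group comparison, 20 per group gives 54% to 56% power two-sided. That is a separate matter. It matters here only because it shows that precision is scarce.

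**Formula for the gain.** Let r be the correlation of one early score with follow-up, and rb the correlation between the two early scores. Both are assumptions, because the document gives neither. The two scores are taken as equally predictive.

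- Residual variance with one baseline: v1 = 1 − r²
- Residual variance with the mean of two: v2 = 1 − 2r²/(1 + rb)
- SE ratio: √(v2/v1)

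Example, r = 0.7 and rb = 0.8: v1 = 0.51; v2 = 1 − 0.98/1.8 = 0.456; v2/v1 = 0.893; √0.893 = 0.945. The SE falls by 5.5%.

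Required n below is 35.3 × v, rounded up. Power is for 20 per group, two-sided, by normal approximation.

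| r | rb | v1 | v2 | Variance reduction | SE reduction | n per group | Power at 20 per group |
|---|---|---|---|---|---|---|---|
| 0.5 | 0.95 | 0.750 | 0.744 | 0.9% | 0.4% | 27 → 27 | 68.2% → 68.6% |
| 0.5 | 0.80 | 0.750 | 0.722 | 3.7% | 1.9% | 27 → 26 | 68.2% → 69.9% |
| 0.6 | 0.90 | 0.640 | 0.621 | 3.0% | 1.5% | 23 → 22 | 75.0% → 76.3% |
| 0.7 | 0.95 | 0.510 | 0.497 | 2.5% | 1.2% | 19 → 18 | 83.9% → 84.8% |
| 0.7 | 0.80 | 0.510 | 0.456 | 10.7% | 5.5% | 19 → 17 | 83.9% → 87.8% |
| 0.8 | 0.80 | 0.360 | 0.289 | 19.8% | 10.4% | 13 → 11 | 94.0% → 97.5% |

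Over r 0.5 to 0.7 and rb 0.8 to 0.95, the SE falls by 0.4% to 5.5%, required n by 0 to 2 per group, and power at 20 rises by 0.4 to 3.9 points. The n and power columns treat 3 points as the unadjusted SD and residents as independently randomized. They show the change between the two models and do not estimate this trial's power.

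**Ceiling.** If the same test is equally reliable each time and differs only by measurement error, rb is its reliability and r cannot exceed rb. The last row sits on that limit: it needs true function to keep the same ranking through 24 weeks of intervention.

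**Clustering.** Nursing homes are randomized. Let s be the share of an arm mean's variance, under the one-baseline model, that comes from home-to-home differences the second score does not remove. The SE ratio becomes √(s + (1 − s) × v2/v1). At s = 0 this is the table's result. As s rises it moves toward 1, so the reductions above are upper values for this design.

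**The case against.** The strongest reply is that nothing here is wrong: one pre-treatment value of the outcome is a standard and valid covariate, and a second is a matter of preference. That stands as far as validity goes. A reader might infer that the planned SPPB comparison is biased or mis-specified, and the document does not support that.

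A reader might also infer that the enrollment score is thrown away. The text does not say so. It does not explain how the baseline value is formed when two scores exist, and the open list of confounding factors could admit another. Early functional testing has other stated uses too: stratifying the randomization and assigning the exercise programme. What remains is that the singular rule, read beside a column named Baseline, most naturally means one score.

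The two ticks may also be one assessment entered in two columns, since the recruitment text speaks of an initial assessment and gives no interval. If so, there is no gain and nothing to change. If the tests are separate and the later one predicts better, equal weighting overstates what the earlier one adds.

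Two larger claims fail. One is a residual variance reduction of up to 25%. That needs reliability 0.75 with a baseline-to-follow-up correlation of 0.80, which equal reliability at both times rules out, because the correlation could not exceed 0.75. The other is that the second cognitive score sharpens the primary comparison. It bears only on the secondary cognitive outcome.

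Finally, Table 2's column order might suggest that baseline SPPB is taken after allocation. The randomization text says the opposite, so this is an inconsistency to settle and does not show that single-baseline adjustment is wrong.

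**Conclusion.** The point holds as a free improvement of minor severity. The planned adjustment is sound, but a second pre-allocation SPPB score appears to be scheduled and has no stated place in the model. Under the assumed correlations the loss is about 0.4% to 5.5% of the standard error, about 10% at the outer limit, and less once between-home variance is counted.

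The conclusion rests on two conditions that the article does not settle: that the two ticks are separate measurements, and that both precede allocation.

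**What to change.** 1. Reconcile the order of allocation and baseline in Table 2 with the Randomization and blinding section, and state whether the enrollment and baseline ticks are separate measurements.
2. If they are separate and both precede allocation, add one sentence to the Statistical analysis section: for any outcome measured separately at enrollment and at baseline before allocation, both scores, or their mean, enter that outcome's model. Outcomes first measured at baseline keep the single value.
3. If the baseline test turns out to follow allocation, use only the enrollment score as the covariate. Residents will know their group by then, and SPPB depends on effort.

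The cost is one sentence and no new measurement. Two separate covariates take one extra degree of freedom; the mean takes none.
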